### Missing data

Other than antibiotics, outcome data and variables for adjustment are based on routine electronic health records linked by NHS numbers within participating organisations. As these records are used for patient management, data in the variables being requested should not be missing. As above, for mortality, data will be considered to be completely ascertained; similarly, for other outcomes, as follow-up time is relatively short, observed data will be assumed to represent all events within the prescribed follow-up time (30–90 days).

For adjustment variables, first if demographics are missing for only some records for a patient, these will be carried forwards and backwards to any other records with missing values. Afterwards, any records with missing values for any of the key adjustment variables will be enumerated. If these comprise < 0.1% of records from an organisation, they will be assumed to represent incorrect records in the underlying data sources and checked with the individual organisation, but will be dropped from all analyses (adjusted and unadjusted). Where records with missing data comprise > 0.1% of records from an organisation, this will be queried, since it is not anticipated that this should ever occur with the data items above.

### Health economics

A within-trial cost-effectiveness analysis will estimate and compare the costs and impact of ‘review and revise’ compared to standard care. The primary analysis will take an NHS perspective based on data collected within the phase III main trial and supplemented with data from the literature where necessary (e.g. quality-of-life estimates). Costs of inpatient stays will be obtained from the Reference Costs Database (DH). Intervention costs will be estimated from admission and antibiotic data collected in the main trial. Costs of antibiotics used will be estimated from the British National Formulary Drugs and pharmaceutical electronic market information tool (eMIT) for generic antibiotics, and actual costs (negotiated locally) obtained from participating organisations (purposively sampled based on size and type). Collecting such detailed information on actual antibiotic costs is important, because whilst we expect that the intervention would lead to lower antibiotic use, and hence reduced costs, this is not necessarily the case. It might lead to more confidence in prescribing antibiotics initially (e.g. following ‘Surviving Sepsis’ [26]) with appropriate discontinuation at early review. Costs of tests (e.g. C-reactive protein) and investigations (e.g. magnetic resonance imaging (MRI), ultrasound) will be estimated in these same organisations.

Providing the main trial demonstrates the intervention is non-inferior for 30-day mortality and superior for antibiotic usage, we will compare the mean per-patient costs, pre- and post-intervention implementation, and calculate the difference, and then estimate the incremental cost per percentage reduction in antibiotic usage (overall and by organisation). We will then explore alternative thresholds to examine the maximum willingness to pay for a reduction in hospital stays, admissions (and emergency re-admissions), infection recurrences and quality-adjusted life years gained. A strategy will be deemed cost-effective if the incremental cost-effectiveness ratio is under this threshold. Probabilistic sensitivity analysis will address the joint contribution of parameter uncertainty on decision uncertainty and provide adequate estimates of expected cost and effects. This primary analysis will take an NHS perspective based on resource use within secondary care. Differences in resource use outside of hospital are implicitly assumed to be equal before and after the intervention, and therefore excluded from modelling.

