To evaluate the cost-effectiveness of the behavioural intervention	Resource utilisation and costs	Over the current admission and up to 30 days post-discharge
To quantify uptake and acceptability of the online training component of the behavioural intervention (process outcome)	Proportion of locally identified and pre-specified essential individuals who drive prescribing decisions for acute/general medical inpatients at the organisation who complete the online training (recorded electronically by individuals entering their name and work (NHS) email on the last page) or on an attendance list if the local organisation has opted to do face-to-face training sessions	Within 3 months of invitation to complete training
To quantify uptake of the ARK ‘review and revise’ procedure within the behavioural intervention (process outcome)	Proportion of regularly audited antibiotics prescriptions which document the ARK classification criteria Proportion of regularly audited antibiotics prescriptions which are stopped at ‘review and revise’	Over 12 weeks following implementation date

^a^In organisations with individual electronic prescribing (rather than bulk) antibiotic data

Note: WHO definitions of ’Access’, ’Watch’ and ’Reserve’ antibiotics will be used, following the 2017 Essential Medicines List, using the PHE interpretation. Broad-spectrum is defined as co-amoxiclav; piperacillin/tazobactam; second (e.g. cefuroxime), third (e.g. ceftriaxone ceftazidime) or fourth (e.g. cefepime) generation cephalosporins or cephalosporin-beta-lactamase inhibitor combinations (e.g. ceftazidime-avibactam, ceftolozane-tazobactam); carbapenems; quinolones; azithromycin; tigecycline; aztreonam; and telithromycin. Cefaclor is not included as a second generation cephalosporin because it is administered orally and is not well absorbed

Process evaluation will also include interviews/focus groups with healthcare professionals, a brief questionnaire concerning healthcare professionals’ perceived barriers to review and revise (collected online on completion of the online training and 1 month later) and healthcare professionals’ usage of the online training (collected automatically by the website and mobile software). Implementation of ARK will also be assessed using a questionnaire completed by the ARK champion.

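### Intervention costs are to come from admission and antibiotic data, which hold none of the cost of delivering ARK, so the incremental cost is biased towards ARK by an amount the protocol cannot supply

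*Protocol article*

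**What the plan says.** Table 1 lists a tertiary objective: "To evaluate the cost-effectiveness of the behavioural intervention". Its measure is resource use and costs, with the time window "Over the current admission and up to 30 days post-discharge".

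The Health economics section gives one source for the cost of the intervention: "Intervention costs will be estimated from admission and antibiotic data collected in the main trial". The other costs it names are inpatient stays, antibiotics, and tests and investigations in sampled organisations. The comparison is then described: "we will compare the mean per-patient costs, pre- and post-intervention implementation, and calculate the difference", followed by a plan to "estimate the incremental cost per percentage reduction in antibiotic usage (overall and by organisation"). On perspective: "This primary analysis will take an NHS perspective based on resource use within secondary care". The comparison is conditional: "Providing the main trial demonstrates the intervention is non-inferior for 30-day mortality and superior for antibiotic usage".

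Elsewhere the article describes what delivery involves. The Intervention section lists the training website, the decision aid, audit with regular team discussions, leaflets, and a toolkit for a champion and implementation team. The Randomisation section adds a 3-month lead-in for assembling the team and meeting staff. The fidelity criteria under Statistical analysis add changes to drug charts or e-prescribing, and continuing audit and feedback.

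**The concern.** The source named for intervention costs cannot supply them. An inpatient record or an antibiotic total does not show how long staff spent in training, how many hours the champion worked, or what it cost to change a drug chart. Hospital staff time of this kind is an NHS secondary-care cost, so the chosen perspective gives no reason to leave it out.

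At stake is the cost-effectiveness result that hospitals would read when deciding whether to adopt ARK. A ratio without the programme's own delivery cost flatters the programme. The ratios by organisation would also ignore differences in implementation effort.

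**Working it through.** **Is delivery cost covered anywhere?** The cost items, set beside the delivery inputs:

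- Inpatient stays (national reference costs): patient care.
- Antibiotics (formulary, generic and local prices): patient care.
- Tests and investigations: patient care.
- Intervention costs: assigned to admission and antibiotic data, which record patient care.
- Table 1 window: admission to 30 days after discharge. This follows a patient episode and does not naturally hold work done in the 3 months before implementation.

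Training, champion and team time, audit and feedback, chart or e-prescribing changes, and leaflets match none of these.

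**Direction.** Let ΔC be the true difference in mean cost per admission (post minus pre), D the additional delivery cost per admission, and R the percentage reduction in antibiotic use.

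- True ratio = ΔC / R
- Ratio as planned = (ΔC − D) / R
- Error = −D / R

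D is positive, since it arises only because of ARK. R is positive overall, because the comparison is made only if antibiotic use has been shown to fall. The planned ratio is therefore too low. In a single organisation R need not be positive. There the incremental cost is still understated, but the ratio itself needs separate interpretation.

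**Size.** The article states no cost, ratio or threshold, so there is no figure to reproduce. What follows is illustration only.

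Inputs from the Sample size section are 35 organisations averaging 10,000 admissions a year (uniform 5000 to 15,000), one of 25,000, and a 15% reduction.

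- Mean admissions = (35 × 10,000 + 25,000) / 36 = 10,417 per organisation per year.
- Follow-up after implementation: 12 months for the last organisation. For the first main-trial organisation (12 February 2018 to 24 June 2020) it is about 28.4 months, or 10,417 × 28.4 / 12 = 24,653 admissions.

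Delivery costs per organisation are assumed:

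| Assumed cost | Per admission, 12 months | Per admission, 28.4 months | Ratio understated, per percentage point (12 / 28.4 months) |
|---|---|---|---|
| £5,000 | £0.48 | £0.20 | £0.03 / £0.01 |
| £20,000 | £1.92 | £0.81 | £0.13 / £0.05 |
| £50,000 | £4.80 | £2.03 | £0.32 / £0.14 |
| £100,000 | £9.60 | £4.06 | £0.64 / £0.27 |

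The last column is D / 15.

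For scale, the simulated prescribing rate is read here as 1500 to 3000 DDDs per 1000 admissions; the wording is unclear, but this fits the unit used later in the same paragraph. A 15% cut saves 0.15 × 1.5 = 0.225 to 0.15 × 3.0 = 0.45 DDD per admission. At an assumed £1 to £5 per DDD, that is £0.23 to £2.25. The two ranges overlap.

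Break-even: an apparent saving of £1 per admission would vanish at a delivery cost of about £10,400 per organisation over 12 months, or about £24,700 over 28.4 months.

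**The case against.** The strongest reply is that intervention costs here means the cost of care under the intervention. The sentence sits between stay costs and antibiotic costs, and the comparison is of per-patient costs, for which those records are the natural source. The complaint would then be one of silence in a condensed article whose full protocol is not shown. This reading is possible but does not repair the plan: delivery cost would still be absent from the per-patient comparison described. The allowance for supplementing trial data from the literature does not fill the gap either. Its only example is quality of life, and nothing assigns delivery cost to it.

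Three other points stand. First, every unit cost above is assumed, and the drug saving is only part of the incremental cost. Changes in stay costs could outweigh both it and delivery. Second, standard care already contains some review activity: the Background cites compliance monitoring in 48% of trusts answering a 2013 survey. Gross audit time would therefore overstate the additional cost. Third, the objective is tertiary and the comparison depends on success on both co-primary outcomes.

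A reader might infer that delivery cost equals or exceeds the drug saving, or that its omission turns a net cost into an apparent saving. The documents do not support either. Both depend on assumed prices and on the period over which delivery is spread, and both leave out stay costs.

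**Conclusion.** The point holds. Followed as written, the plan leaves the cost of delivering ARK out of the incremental cost and biases the overall cost per percentage reduction in ARK's favour. The direction rests only on delivery cost being positive and on antibiotic use having fallen, which the plan requires before making the comparison.

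The size is unknown. The illustrated £0.20 to £9.60 per admission rests on assumed costs of £5,000 to £100,000 per organisation and on the simulation's admission rates. It may be small or comparable to the drug saving. Nothing here touches the co-primary outcomes or the trial's main conclusion, and the documents do not show that the cost-effectiveness conclusion would be reversed.

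**What to change.** Replace the sentence on intervention costs with a statement that delivery costs are estimated per organisation from:

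- training completions and audit submissions, which are already recorded;
- a few time-use items (champion, implementation team, audit and feedback, chart or e-prescribing changes, leaflets) added to an existing instrument: "Implementation of ARK will also be assessed using a questionnaire completed by the ARK champion".

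The text should also state that:

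- only activity additional to standard care is counted;
- research-only costs are excluded, such as the £14,000 per organisation for data extraction;
- all delivery cost, including that between randomisation and implementation, is charged to the intervention side and spread over post-implementation admissions. Placing it in the preparation months would load it onto the pre-implementation comparator and shrink the difference again;
- the period of spreading is fixed in advance, since 12 against 28.4 months changes the per-admission figure by 28.4 / 12 = 2.4 times;
- delivery cost is varied in the planned probabilistic sensitivity analysis.

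The cost is a few questionnaire items and some analyst time. Hours will carry recall error, most of all in organisations randomised early (from November 2017), and the ratio will look less favourable.

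### The cost-effectiveness comparison is run only if both co-primary outcomes succeed, so a stated objective can go unanswered when the mortality interval misses its limits

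*Protocol article*

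**What the plan says.** Table 1 of the protocol article lists, among the tertiary objectives, "To evaluate the cost-effectiveness of the behavioural intervention", with resource use and costs as the measure and no condition attached. The Health economics section opens in the same way: "A within-trial cost-effectiveness analysis will estimate and compare the costs and impact". It adds that lower antibiotic use need not mean lower cost, because the intervention might make clinicians readier to start antibiotics. It also plans to collect locally negotiated antibiotic costs and the costs of tests and investigations.

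The next paragraph of that section sets the condition: "Providing the main trial demonstrates the intervention is non-inferior for 30-day mortality and superior for antibiotic usage, we will compare the mean per-patient costs". The difference in mean cost, the cost for each percentage by which antibiotic use falls, and the exploration of willingness-to-pay thresholds are then listed in sequence. The thresholds cover hospital stays, admissions, "infection recurrences and quality-adjusted life years gained". The same paragraph continues: "Probabilistic sensitivity analysis will address the joint contribution of parameter uncertainty on decision uncertainty". No economic analysis is described for a trial in which either co-primary fails.

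The Sample size section defines non-inferiority by two limits: the whole 95% confidence interval for the relative change in mortality must lie within 0.95 to 1.05. It claims more than 85% power.

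**The concern.** An economic evaluation estimates costs and effects together with their uncertainty, and its usefulness does not depend on passing a significance test. Failing to show non-inferiority is not evidence of harm; it may mean only that the interval is too wide. That is when an analysis of decision uncertainty is most informative, and it is when this plan withholds it.

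Three features of the article make the condition awkward. Cost-effectiveness is stated as an objective in its own right. The direction of the cost effect is acknowledged to be open. And the Data sharing and dissemination section says that a post-trial version of the intervention is already freely available to NHS organisations, so they may adopt it, and need its costs, whatever the co-primary results.

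The two-limit definition of non-inferiority adds an oddity. Read literally, a mortality benefit large enough to take the lower confidence limit below 0.95 also switches the economics off.

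**Working it through.** **Inputs.** Limits 0.95 and 1.05, two-sided 95% interval, power above 85% (Sample size section); no true mortality effect under the planning model (same section). The article gives no standard error, so I assume power of exactly 85% at a true relative risk (RR) of 1.00 and a normal estimate on the log scale.

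**The plan's own figure.** The stated power cannot be reproduced uniquely, because it is an inequality and several simulation settings are open to interpretation. Simulating the described design gave two-limit power for mortality of 100%, 95%, 89% or 67%, depending on the between-month standard deviation, the length of the pre-period and whether trends are fitted. It gave 0% if the standard deviation of 0.1 is read on the probability scale. Superiority for antibiotic use was 100% in every setting. So the mortality condition is the one that matters here, and 85% serves as the protocol's own floor.

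**Standard error implied by 85% power.** Log limits: ln 0.95 = −0.0513 and ln 1.05 = 0.0488. Solve for the SE s in

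Φ((0.0488 − 1.96s)/s) − Φ((−0.0513 + 1.96s)/s) = 0.85,

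which gives s = 0.0147.

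**Estimates that pass.** The log estimate must lie between −0.0513 + 1.96 × 0.0147 = −0.0225 and 0.0488 − 1.96 × 0.0147 = 0.0200, that is, an estimated RR between about 0.978 and 1.020.

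**Probability that the mortality condition is met.** P = Φ((0.0200 − ln RR)/0.0147) − Φ((−0.0225 − ln RR)/0.0147).

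| True RR | Condition met | Economics withheld |
|---|---|---|
| 0.97 | 0.29 | 0.71 |
| 0.98 | 0.56 | 0.44 |
| 1.00 | 0.85 | 0.15 |
| 1.01 | 0.74 | 0.26 |
| 1.02 | 0.50 | 0.50 |
| 1.03 | 0.26 | 0.74 |

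For RR 0.97: ln 0.97 = −0.0305, so P = Φ(3.43) − Φ(0.54) = 0.9997 − 0.7063 = 0.29.

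**If only the upper limit counted.** Then s = 0.0488/(1.96 + 1.036) = 0.0163. The condition is met with probability 0.85 at RR 1.00, 0.43 at 1.02 and 0.99 at 0.98. The loss under benefit then disappears, and the loss under slight harm remains.

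**Selection of the mortality estimate.** Given that the condition is met, the mean estimate under the two-limit rule (truncated normal) is 0.999 at true RR 1.00, 1.008 at 1.02, 1.011 at 1.03 and 0.990 at 0.98. The pull is towards no effect from both sides, with essentially none at RR 1.00. This matters only if the trial's mortality effect is an input to the economic model.

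**The case against.** The best defence is that the condition is a deliberate choice of scope. The section on outcomes says the intervention has failed if it does not reduce antibiotic use, and that success requires both co-primaries. A cost for each percentage fall in antibiotic use means little if there is no fall. A general aim followed by a specific condition is ordinary drafting rather than a contradiction. The main resource components (length of stay, ICU admission, re-admission and antibiotic use) are analysed in any case. The power claim is above 85%, so 15% at RR 1.00 is a ceiling.

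Much of this stands. The ratio is a poor summary when its denominator is near zero, the resource components will be reported, and the 15% is an upper bound under the protocol's claim. But a rule for success can govern interpretation without governing whether costs are estimated. Uncosted components also do not answer an objective framed as cost-effectiveness.

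A reader might go further and infer that the condition makes the economic result look safer than it is, because only favourable mortality estimates reach the model. The article does not support that. It nowhere says that trial mortality enters the economic model. The ratio it names uses antibiotic use as the effect. Quality-adjusted life years appear only in the threshold work, their derivation is not described, and quality-of-life values may come from the literature. Even if mortality did enter, the two-limit rule produces essentially no bias at RR 1.00 and shrinks a true benefit as well as a true harm.

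**Conclusion.** The point holds as a minor one. Followed as written, the plan leaves a stated tertiary objective unanswered whenever either co-primary fails, including after a narrow miss on mortality or a mortality benefit that breaches the lower limit. On the mortality condition alone the loss is up to 15% of trials at a true RR of 1.00, about 50% at 1.02 and about 71% at 0.97. These figures assume exactly 85% power, a normal estimate on the log scale and the literal two-limit rule; higher actual power would reduce them. The 71% depends wholly on the lower limit being applied.

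Distortion of the mortality estimate is a conditional remark and not part of the finding. Only if trial mortality feeds the quality-adjusted life years would a true 1.02 appear as about 1.008 among trials that pass. No primary or secondary estimate, test or safety conclusion is affected.

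**What to change.** Delete the opening condition from the second paragraph of Health economics. State that costs, effects with their uncertainty and the probabilistic analysis will be reported whatever the co-primary results, and that only the declaration that the strategy is cost-effective depends on both co-primaries succeeding. Where antibiotic use is not clearly reduced, present the cost and effect differences jointly and do not rely on the ratio. Add a sentence saying whether, and how, the trial's mortality effect enters the quality-adjusted life years.

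The cost is a few sentences in the protocol or health economics plan. No new data are needed, since resource use and costs are already to be collected. The one downside is some analysis work even if the intervention fails.

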### Follow-up

The intervention is delivered to healthcare professionals involved in prescribing or administering antibiotics, but outcomes are assessed in inpatients admitted to acute/general medicine (see the following section). Therefore, follow-up periods relate to calendar time before and after implementation intervention. Routinely collected electronic patient health data are therefore requested from each organisation from 1 February 2016 (2 years before the start of phase III), or as close to this as possible (or up to 2 years pre-implementation for feasibility and pilot organisations). Final data will be requested on 31 October 2020, 15 months after the last randomised implementation date, to allow 90-day mortality to be ascertained on the last patients admitted up to 12 months’ post the last randomised implementation date.

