For analyses comparing periods before and after introduction of the intervention, we hypothesise that the intervention could produce either a step change in each outcome, or ongoing changes over time (i.e. an interaction between intervention vs control and calendar time), or both. Analysis will therefore use an interrupted time series (ITS) analysis which not only estimates whether the intervention has a direct immediate impact, but also whether it has any impact on year-on-year trends after implementation (and compared with year-on-year trends pre-implementation) (Fig. 2). For example, even if there is no immediate impact of the intervention on mortality, it will be particularly important to monitor, say, whether any calendar year trends suggest mortality increases post-implementation. It will also be important to monitor whether antibiotic use declined faster post- vs pre-implementation.

Other reasons for using the ITS approach within organisation, and then pooling organisation-level estimates, are that many other things are likely to be changing differently in different organisations, and within organisations, over calendar time. For example, financial incentives could be introduced to reduce antibiotic use in hospital and increase the numbers of antibiotic prescriptions that receive review (under the Commissioning for Quality and Innovation [CQUIN]) payments framework). These external factors will affect within-organisation comparisons less than between-organisation comparisons. Further rates may not be constant before or after the intervention. Finally the calendar-time blocked randomisation makes the assumptions underlying the standard vertical comparisons (between organisations already randomised to intervention vs not at each step) more questionable. The date of introduction of the intervention will be the planned date of implementation for the feasibility and internal pilot organisations and the date that each organisation was randomised to implement the intervention in the main trial. Sensitivity analyses for the main trial will also consider the fact that implementation may occur gradually over approximately 3 months [56], by incorporating a trend for the 3 months post-implementation date instead of a single step change at the implementation date. The DMC will be asked to advise on the most appropriate analysis model as part of their Charter.

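### The cost comparison is stated as a plain before/after difference in mean cost with no trend term, although the protocol adopts interrupted time series for before/after comparisons because rates may not be constant

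*Protocol article*

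**What the plan says.** Health economics (protocol article): once the trial has shown non-inferior mortality and lower antibiotic use, "we will compare the mean per-patient costs, pre- and post-intervention implementation, and calculate the difference". The next step is to "then estimate the incremental cost per percentage reduction in antibiotic usage", both overall and by organisation. The section names no trend term, calendar-time term or case-mix adjustment, and no analysis window beyond data from the phase III main trial. It plans a probabilistic sensitivity analysis for parameter uncertainty. Table 1 lists resource use and costs as a tertiary outcome, measured "Over the current admission and up to 30 days post-discharge".

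Statistical analysis: for comparisons of the periods before and after introduction, "Analysis will therefore use an interrupted time series (ITS) analysis which not only estimates whether the intervention has a direct immediate impact"; it also estimates the change in trend. Among the reasons given are that "many other things are likely to be changing differently in different organisations, and within organisations, over calendar time" and that "Further rates may not be constant before or after the intervention". Each outcome is to be modelled within each organisation as a pre-trend, a step and a post-trend, and the estimates are then pooled by meta-analysis.

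**The concern.** A difference between two period means assumes that, without the intervention, mean cost would have been the same in both periods. The Statistical analysis section is not willing to assume that of rates in general. The cost of an admission is built largely from inpatient stay and antibiotics, both of which are trial outcomes that get a trend-adjusted model. As written, the stay would be analysed with a trend and the cost of the same stay without one. The trial could then report no effect on length of stay beside a cost saving that comes only from a pre-existing decline in stay.

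Randomising the implementation date does not remove this. The comparison is within organisation and the post period always follows the pre period, so a common drift has the same sign everywhere and does not cancel on pooling. Probabilistic sensitivity analysis does not help either, because it propagates uncertainty in the parameters and not confounding by time. At stake is the incremental cost, and through it the ratio and any statement that the strategy is cost-effective.

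**Working it through.** **Inputs from the protocol article**
- Start of data: 1 February 2016, or as close as possible (Follow-up).
- First and last main-trial implementation: 12 February 2018 and 24 June 2019 (Design).
- End of follow-up: 12 months after the last implementation, estimated June 2020 (Fig. 3 caption); 24 June 2020 is used here.
- Study length: 4.5 years (Data sharing and dissemination).
- Annual drift in cost: not given. Assumed 1% to 3% a year.

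**Check on the window.** From 1 February 2016 to 24 June 2020 is 4.39 years, within 3% of the stated 4.5. Running to 31 July 2020 gives 4.50.

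**Distance between the periods.** With start S, implementation T, end E and even accrual, the pre midpoint is (S+T)/2 and the post midpoint is (T+E)/2. The gap is (E−S)/2, whatever T is.
- First implementer: pre 2.03 years, post 2.36 years; gap (2.03 + 2.36)/2 = 2.20 years.
- Last implementer: pre 3.39 years, post 1.00 year; gap (3.39 + 1.00)/2 = 2.20 years.
- With an end date of 31 July 2020 the gap is 2.25 years.

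**Spurious difference with no true effect.** For annual drift g it is about (1+g)^2.2 − 1:

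| Assumed drift per year | Spurious difference in mean cost |
|---|---|
| 1% | 2.2% |
| 2% | 4.5% |
| 3% | 6.7% |

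A negative drift gives a spurious saving of similar size. The only background trend in the article is a 7% rise in hospital prescribing over 2013–2018. Taken as five years this is 1.07^(1/5) − 1 = 1.36% a year, which over 2.2 years gives 3.0%. That is a trend in prescribing, not in cost, so it serves only as an illustration.

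**Carry-over into the ratio.** If the antibiotic reduction equals the 15% target, the error per percentage point of reduction is 2.2/15 = 0.15% to 6.7/15 = 0.45% of mean admission cost.

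**Simulation.** Monthly cost series for 36 organisations were simulated with log-linear drift, no intervention effect, an assumed 2% monthly noise and evenly spread implementation dates:

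| Drift per year | Difference in means | ITS step (SE) | ITS slope change per year (SE) |
|---|---|---|---|
| 1% | 2.2% | −0.25% (0.23) | −0.07 points (0.22) |
| 1.36% | 3.0% | 0.24% (0.22) | −0.15 points (0.23) |
| 3% | 6.9% | 0.09% (0.20) | 0.10 points (0.19) |

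The interrupted time series is correctly specified here by construction, so this shows what it removes when drift is smooth, not that it removes every time effect. Limiting post data to 12 months per organisation shortens the gap for early implementers but does not abolish it: at 1% drift the difference in means was still 1.8%.

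**The case against.** The strongest reply is that the Health economics sentence names a contrast and not an estimator. The article uses similar before/after shorthand for mortality, which plainly goes through the time series model. The Statistical analysis section introduces that model for analyses comparing periods before and after introduction and then says each outcome is modelled this way. Costs appear in Table 1 as an outcome measure, and results overall and by organisation fit the same structure. Modelling detail for a tertiary objective is also what a condensed article leaves to the full protocol or analysis plan.

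This reading is possible. But the Health economics section neither refers to that model nor describes it. It gives its own steps: take the means before and after, then the difference. At best the two sections need reconciling, and the remedy is the same.

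Other parts of the reply stand, and they bar stronger inferences that a reader might draw:
- **That the protocol says rates or costs drift.** It says only that rates may not be constant and that other things are likely to be changing.
- **That the protocol rejects before/after comparison because of financial incentives.** It uses incentives to prefer within-organisation over between-organisation comparison.
- **That the ratio certainly mixes two methods.** No method is stated for the antibiotic reduction in the denominator. The mismatch arises only if that figure is taken from the time series model.
- **That the 2.2-year gap holds for every organisation.** Data may start later than February 2016, feasibility and pilot sites have a different pre period, and the economic window is not stated.
- **That price inflation is part of the error.** It would not be if all admissions were costed at one price year, which the article does not settle. Drift in stay, case mix or antibiotic use would remain.

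**Conclusion.** The point holds in a limited form. The cost comparison is stated without a trend term, in a protocol that adopts trend-adjusted models for before/after comparisons because rates may not be constant. If it is followed as written over the whole data window, an assumed drift of 1% to 3% a year in resource use gives a spurious cost difference of roughly 2% to 7% of mean cost.

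That range rests on the assumed drift, even accrual, and organisations supplying data from February 2016 to June 2020. The documents do not support saying that a bias of this size, or in a given direction, will occur. Nor do they give an expected cost effect to set it against, so whether it would change the cost-effectiveness conclusion cannot be judged. The objective is tertiary and its ratio is computed only if both co-primary aims are met, so the mortality and antibiotic conclusions are untouched. It should still be corrected, because the text is inconsistent and the remedy is cheap.

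**What to change.** In Health economics, replace the comparison of period means with a statement that:
- incremental cost per admission is estimated with the organisation-level step-plus-trend model and pooling in Statistical analysis;
- the model is fitted so that the result is a difference in mean cost, as the ratio requires;
- all admissions are costed at one price year;
- the cost effect is evaluated at the same post-implementation time as the antibiotic effect in the ratio, and that antibiotic effect comes from the same kind of model.

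Keep the raw before/after difference as descriptive only, and state the data window.

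If the intention was always that the general method covers costs, a cross-reference with the price year and evaluation time is enough. The cost is a change of wording and one more outcome through an existing model, with no new data or design change. Intervals will be somewhat wider than for a difference of means, most visibly in the by-organisation estimates.
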